# The Patient Activation through Community Empowerment/Engagement for Diabetes Management (PACE-D) protocol: a non-randomised controlled trial of personalised care and support planning for persons living with diabetes

**DOI:** 10.1186/s12875-020-01173-2

**Published:** 2020-06-19

**Keywords:** Care and support planning, *Patient activation.*, *Self-management.*, *Diabetes mellitus.*, *Long term conditions.*, *Primary care.*

## Abstract

**Background:**

Personalised care and support planning (CSP) has been shown to improve diabetes outcomes, patient experience and provider morale in the care of persons living with diabetes. However, this has not been confirmed in controlled studies. Patient Activation through Community Empowerment/Engagement for Diabetes Management (PACE-D) is a pragmatic controlled trial that evaluates the effectiveness of personalised CSP in persons living with diabetes in the public primary care setting in Singapore.

**Methods:**

Teamlet-empanelled patients with diabetes at four polyclinics are recruited for this study. Participants who attend either of the two Intervention clinics are sent their investigation results in a care planning letter (CPL) to *prepare* them for the CSP conversation. This conversation is facilitated by a trained CSP practitioner who engages them in *discussion* of concerns, goals and action plans, and *documents* their plans for subsequent *review*. Participants in the two Control clinics will receive standard diabetes care. Participants will complete two or more CSP conversations (Intervention) or regular consultations (Control) at the annual review visits within the 18 months of the study. The sample size is calculated at 1620 participants, with glycated haemoglobin (HbA1c) as the primary outcome measure. Secondary outcome measures include patient activation (as measured by PAM-13) and changes in healthcare utilisation and cost.

**Discussion:**

This study is a pragmatic trial that evaluates the effectiveness of personalised CSP in persons living with diabetes in a real world setting. It promises to provide insights with regard to the implementation of this model of care in Singapore and the region.

**Trial registration:**

ClinicalTrials.gov Identifier NCT04288362. Retrospectively registered on 28 February 2020.

## Background

With more than 60% of the 422 million persons living with diabetes mellitus, Asia is poised to be the global epicentre of this long term condition (LTC) in this century [1, 2]. Inhabited by 5.7 million residents and nestled within Southeast Asia, the multicultural city-state of Singapore is a microcosm of the sociocultural norms of the region. Given a prevalence of 11.3% among adults in 2010, Singapore has one of the highest rates of diabetes worldwide [3, 4]. Current estimates predict that one million residents will have diabetes in 2050 compared to 440,000 in 2014 [5, 6]. Healthcare cost-wise, USD 1.9 billion will be spent on diabetes in 2050 compared to USD 790 million in 2010 [7]. In response to these projections, Singapore declared a nationwide, long-term “war on diabetes” in 2016 [8]. Support for active self-management of persons living with diabetes was identified as a key focus of the campaign [5].

Over the past decade, it has been increasingly recognised that outcomes for persons living with diabetes and for the healthcare system, are better when persons with LTCs are empowered to take charge of their condition [9, 10]. In Singapore, however, the public primary care clinics (polyclinics) have been designed mainly for efficient medical problem solving rather than for systematic engagement of patients in long-term self-care. As an illustration, a typical consultation for an LTC at the polyclinic lasts 8–12 min, usually used to address new complaints, explain investigation results, problem-solve, provide patient education, and plan subsequent steps. The presence of comorbidities compounds the time-pressure. Most patients and doctors would find it difficult to consider the significance of adopting any positive health behaviour within the time constraints. Given that the bulk of patients with LTCs including diabetes are managed at the polyclinic, there is value in learning and adapting from best practices elsewhere [4].

### Personalised care planning

Persons with LTCs have important roles in managing their own health in the context of their daily lives, but often need support, including to develop the confidence and skills to adhere to medications, adopt and maintain healthy lifestyles, and know when and how to seek medical advice. Personalised care and support planning (CSP) has been proposed as a means to provide support from healthcare providers (HCPs) that is individualised to the needs of specific persons with LTCs and oriented to enable them not just to manage their LTCs well in biomedical terms but more broadly to live well with those LTCs [11, 12]. Personalised CSP entails a conversation or a series of conversations between the patient and the HCP when they jointly agree on goals and actions for managing the patient’s health problems [11, 12]. Evidence shows that personalised care planning, most effective when integrated in routine clinical practice, leads to improvements in certain indicators of physical and psychological health status of patients, and their capability to self-manage their condition as compared to usual care [11, 12].

### The care and support planning model

Year of Care Partnerships (YoC) in the United Kingdom (UK) has implemented and made iterative changes in the use of CSP for over a decade [11, 12]. The personalised CSP has been conceptualised as a meaningful conversation between partners that occurs within a “house of care” [13] with four components: The prepared person living with diabetes and the trained CSP practitioner form each of two walls of the house, the organisational processes that operationalise the CSP form the roof, while institutional support forms its foundation.

YoC’s experience over the past decade has shown that personalised CSPs have resulted in positive outcomes for patients, HCPs and healthcare organisations. Patients experience improved clinical outcomes in terms of glycated haemoglobin (HbA1c) and blood pressure within 3–5 years of enrolment, in parallel with increased engagement with positive health behaviours. Explicit orientation of care to support personal goals in CSPs was observed to raise practitioner morale and strengthen the practitioner-patient relationship; ripple-effects have been seen at the organisational level with improved levels of productivity at zero additional cost [7, 13]. As a further badge of its success, CSP practice has spread to multiple sites across England and Scotland, [11] and CSPs have been adopted as part of the core curriculum in General Practice training in the Royal College of General Practitioners (RCGP) since 2019 [14].

In Patient Activation through Community Empowerment/Engagement for Diabetes Management (PACE-D), the model of care from YoC has been adapted for the Singapore polyclinic context. Structured on the blueprint of the chronic disease model, [15] it places self-management at the forefront of diabetes management. The programme builds on the clinical experience in the management of chronic diseases in the polyclinic setting and on YoC’s extensive experience with the use of care plans. It is underpinned by the conceptual frameworks of the patient-centred consultation, the theories of adult education and self-efficacy, the concepts of self-management and self-empowerment, [9, 16–21] and has been described in terms of six programme theories in a recent realist evaluation [22].

This paper describes the design and significance of PACE-D, a pragmatic controlled trial that evaluates the effectiveness of personalised CSP in persons living with diabetes in the public primary care setting in Singapore.

### Primary objective

The primary objective of this study is to examine the effects of personalised CSP (Intervention) compared to the standard model of care (Control) on glycaemic control, as measured by HbA1c.

### Secondary objectives

The secondary objectives include investigating the change in patient activation [23], measured by Patient Activation Measure-13 (PAM-13), and the difference in healthcare utilisation and cost between the Intervention and Control.

The selection of the primary and secondary objectives reflects strong health policy interests in Singapore. The intervention designers and research team are aware that they can be in some tension with the idea that CSP involves working responsively with each patient to help them manage their life with the condition rather than (more narrowly) to manage the biomedical aspects of the condition well. To elucidate this further, the qualitative experiences of the participants and HCPs will be researched in parallel with this study.

## Methods/design

PACE-D is a pragmatic non-randomised controlled trial that evaluates the effects of personalised CSP on persons living with diabetes over two annual reviews with two groups: Intervention experiences personalised CSP; and Control continues with the current care model. Figure 1 illustrates the flow diagram for study participants.

**Fig. 1 Fig1:**
[figure not shown]
Participant flow in the Patient Activation through Community Empowerment/Engagement for Diabetes Management (PACE-D) study

### Trial oversight

The PACE-D research committee meets quarterly to provide research oversight. Process measures are reported six-monthly to the Ministry of Health (MOH) that funds the project.

### Patient involvement

Feedback from patients recruited in two earlier pilots informed the design of the care planning letter, the length of the questionnaires, and the feasibility of the operational procedures.

### Study setting

PACE-D is conducted in the polyclinics at National University Polyclinics (NUP), the westernmost of three major administrative primary care healthcare groups in Singapore. Each polyclinic is staffed by 15–25 primary care physicians (PCPs) deployed in multi-disciplinary teams which include nurses and clinical pharmacists, with access to the psychologist, dietitian and medical social worker. In addition to the management of acute episodic conditions, the polyclinics provide for the efficient care of the patient with LTCs: laboratory services allow for rapid investigative reporting; surveillance programmes ensure the systematic detection of diabetic retinopathy, neuropathy and nephropathy; and workflows designed to target specific needs through the use of teamlets, [24] tele-consults, [25] and multidisciplinary case discussions [26, 27].

At the polyclinics under NUP, primary care is delivered to patients with LTCs through care teams known as teamlets. Each teamlet provides LTC care to a regular pool of approximately 5000 patients. It is formed by two PCPs and one care manager (CM) who is a chronic disease management-trained senior nurse. These three HCPs are supported by a care coordinator (CC) who schedules consultation and preventive health screening appointments for teamlet-empanelled patients.

In PACE-D, four of the six NUP polyclinics are involved in the study, with two of them designated as Intervention and the other two as Control. In each of these polyclinics, one teamlet is involved in the study and is supported by a PACE-D Coordinator (PC). The role of the PC is to recruit participants and obtain consent for participation, prepare the care planning letter (CPL) for mailing to the participants in the Intervention, and to administer questionnaires to all participants.

### Study population

The study population comprises patients currently receiving care from a designated teamlet in each of the four NUP polyclinics. Patients are recruited if they meet all of the following inclusion criteria: (1) adults with diabetes mellitus aged 21 years old and above; the (2) ability to provide informed consent; (3) ability to communicate in English, Malay or Chinese and (4) ability to comprehend the CPL on their own or with the assistance of family members.

Patients are not eligible for the study if they are (1) pregnant, or unable to engage with the CPL and/or CSP conversation because of any of the following: (2) cognitive impairment; (3) psychotic disorders; and (4) severe hearing/visual impairment.

### Study recruitment process

Each site has a PC who identifies eligible patients in the week’s appointment register. Potential participants are approached to participate in the study by the PC while they are in the waiting area prior to the consult, or by the HCP during the consultation. Consent is obtained from the patients by the PC if they are agreeable to participate. All enrolled patients in both Intervention and Control are each given an SGD $10 voucher by the PC after the completion of every CSP conversation (Intervention) or regular consultation (Control) at the annual review visit during the study.

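### Staff who know the clinic's arm recruit patients one by one, partly through the treating clinician, so selection on readiness to self-manage could differ between arms

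*Protocol article*

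**What the plan says.** Methods/design in the protocol article states that "PACE-D is a pragmatic non-randomised controlled trial". Under Study setting, four polyclinics take part, "with two of them designated as Intervention and the other two as Control", so the arm of every prospective participant is known before anyone is approached. One teamlet per clinic is involved: two physicians and one care manager, supported by a PACE-D Coordinator (PC).

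Under Study recruitment process:

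- Listing: "Each site has a PC who identifies eligible patients in the week’s appointment register".
- Approach: by the PC or by a clinician, "in the waiting area prior to the consult, or by the HCP during the consultation".
- Consent: "Consent is obtained from the patients by the PC if they are agreeable to participate".

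The PC's duties also include to "prepare the care planning letter (CPL) for mailing to the participants in the Intervention", so the recruiter knows the arm. CSP practitioners know it too, because they attended a two-day workshop (Training and support for the healthcare providers).

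The Statistical analyses section commits to intention-to-treat and to baseline HbA1c as a covariate. Other covariates come from the data and the literature and are dropped stepwise at p ≥ 0.2. PAM-13 is collected from everyone at enrolment (Baseline data and questionnaire collection) but is not named as a covariate for HbA1c.

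**The concern.** When clinics are allocated and patients are recruited afterwards by people who know the allocation, the arms can differ in who is invited. Here the plan expressly provides a route in which the clinician decides, in the middle of a consultation, whether to raise the study.

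The motives need not be the same in the two arms. CSP as described under Intervention relies on a prepared patient who sets goals and commits to actions, so an Intervention clinician has some reason to think first of patients who look ready for that. A Control clinician offers the usual review and a brochure and has no corresponding reason.

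Patients who are readier to manage their own condition may do better on HbA1c, PAM-13 and lifestyle measures under either model of care. If they are over-represented in one arm, part of the difference at the second annual review reflects who was invited and not CSP.

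**Working it through.** **1. What the passages establish together**

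- Arm fixed by clinic, not randomised, before any approach: stated (Methods/design; Study setting).
- Recruiters aware of the arm: follows from the PC's role in preparing the letters and from the CSP training.
- A clinician may initiate the invitation: stated (Study recruitment process).
- The inviting clinician may later hold the CSP conversation: inferred. The annual review is with a teamlet clinician (Current model for Diabetes care), but 14 practitioners are trained while two Intervention teamlets hold 2 × 3 = 6 clinicians. Nothing says that the two roles coincide for a given patient.

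**2. What the analysis can correct**

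Intention-to-treat protects comparability after enrolment; this selection happens before it. Baseline HbA1c corrects for starting level, but only partly for motivation or expected change. Baseline PAM-13 would capture some of that, but whether it enters the HbA1c model is left to data-driven selection.

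**3. The plan's own sample size, to obtain a working SD**

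Inputs (Sample size calculation): total 1620, difference 0.5, power 90%, alpha 0.05 (two-sided per Statistical analyses), 6 subgroups, 30% attrition. The SD is not given, so it is solved backwards:

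- Evaluable per arm per subgroup: 1620 × 0.7 / 12 = 94.5
- n = 2 × SD² × (1.96 + 1.28)² / 0.5², so SD = 0.5 × √(94.5 / 2) / 3.24 ≈ 1.06
- Check: SD 1.06 gives 95 per cell, and 95 × 12 / 0.7 = 1629; SD 1.05 gives 93 per cell and 1595. Both are close to 1620.

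The point does not depend on this figure. It only sets a scale for step 4.

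**4. Illustration of size (assumptions, not in the documents)**

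Bias = (excess share of engaged patients in Intervention over Control) × (their extra HbA1c fall whatever the care). Excess shares of 10–30% and extra falls of 0.3–0.5 points are assumed. Evaluable per arm: 1620 × 0.7 / 2 = 567. SE = SD × √(2 / 567), which is 0.063 at SD 1.06 and 0.089 at SD 1.5 (a second assumed value). With no true effect, the two-sided rejection rate is Φ(bias/SE − 1.96) + Φ(−bias/SE − 1.96). Clustering by clinic is ignored.

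| Excess share | Extra fall | Bias (points) | Rejection, SD 1.06 | Rejection, SD 1.5 |
|---|---|---|---|---|
| 10% | 0.3 | 0.03 | 7.6% | 6.3% |
| 10% | 0.5 | 0.05 | 12.5% | 8.7% |
| 20% | 0.3 | 0.06 | 15.9% | 10.3% |
| 20% | 0.5 | 0.10 | 35.5% | 20.2% |
| 30% | 0.3 | 0.09 | 29.8% | 17.3% |
| 30% | 0.5 | 0.15 | 66.4% | 39.1% |

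The nominal rate is 5%. Against the 0.5-point target, the bias is 0.03 / 0.5 = 6% to 0.15 / 0.5 = 30%.

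**5. Room for selection**

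With equal recruitment, 1620 / 4 = 405 per clinic. Against a teamlet pool of about 5000 that is 8.1%, but the pool covers all long term conditions and its diabetes share is not stated. If 20–40% have diabetes (assumption), the pool is 1000–2000 and 405 is about 20–40% of it. If half of those approached consent (assumption), 810 must be approached, about 40–80% of the diabetes pool. The room is real but may be much narrower than 8.1% suggests.

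**The case against.** The trial is openly non-randomised and pragmatic, and some selection risk comes with that. The PC lists eligible patients first and takes consent, and the procedure reads the same for all sites. A consecutive-approach rule or a screening log is also something a journal article may leave to the full protocol. All of this stands, and the silence on such a rule is not the point. The point is the clinician route that the article does state: listing and consent control who is eligible and who signs, not whom the clinician chooses to invite.

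Four stronger readings are tempting but not supported:

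- A reader might infer that clinicians hand-pick participants. The text gives them discretion, most naturally over a list screened by the PC; it does not show that they use it selectively.
- A reader might infer that the eligibility rules themselves work differently by arm, since they refer to patients "unable to engage with the CPL and/or CSP conversation because of any of the following". What follows is a closed list of clinical conditions that applies equally in both arms, and comprehension of the letter may be with family help. This is weak ground.
- A reader might infer that the bias must favour CSP. Clinicians might instead put forward poorly controlled patients who most need help. Control clinics also have the clinician route, and only the difference between arms matters.
- A reader might infer that adjustment cannot help. PAM-13, physical activity, smoking, community resource use and screening attendance are recorded at baseline, so adjustment could remove part of any imbalance. The weakness is that none of these is fixed in the HbA1c model.

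**Conclusion.** The concern holds as a risk of differential selection. Arm-aware staff recruit individuals after clinic designation, and one stated route leaves the invitation to clinicians who may also deliver the intervention. It could bias the HbA1c and PAM-13 contrasts. That it occurs is not shown, a direction favouring CSP is plausible only, and no size can be derived from the documents.

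Under the assumptions set out above, the bias is small beside the target difference but large enough to lift the false-positive rate well above nominal. A change to the recruitment procedure and the HbA1c model is worth making; the documents do not support calling the comparison invalid.

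**What to change.** - **Recruitment.** In Study recruitment process, replace clinician-initiated invitation with one rule for all four clinics: the PC approaches all eligible patients consecutively from the appointment register, before the consult. The consecutive rule matters more than the change of recruiter, because the PC also knows the arm.
- **Record and sensitivity analysis.** Record the approach route for each participant, including those already enrolled where it can be recovered, and pre-specify an HbA1c analysis restricted to participants approached by the PC.
- **Covariate.** Fix baseline PAM-13 in the HbA1c model so that stepwise selection cannot drop it. It is already collected at enrolment.

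The cost is a revised procedure, one data field, one extra analysis and one pre-specified covariate. A PC already screens the register at each site. Recruitment may be somewhat slower, and if the route cannot be recovered for earlier enrolees, the sensitivity analysis will cover only later recruits. The risk is reduced, not removed.

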## Trial intervention

### Current model for Diabetes care

At NUP polyclinics, patients with diabetes undergo an annual panel of laboratory tests in accordance with local clinical guidelines [28]. This includes the HbA1c, fasting capillary glucose, lipid profile, renal function, and urine albumin:creatinine ratio. The patient attends an annual review consultation in the following week with his/her teamlet HCP who jointly reviews the patient and laboratory test results. Depending on the patient’s condition and its control, he/she will be scheduled to attend one or more interim reviews (with laboratory tests performed as indicated) before the following annual review consultation.

### Intervention

In the PACE-D trial, patients enrolled in Intervention undergo personalised CSP. When it works as intended, it entails: [11].
*Preparation* – Two weeks before the scheduled appointment, the patient receives a CPL (Additional file 1) containing his/her most recent laboratory test results and condition-specific information, which act as reflective and agenda-setting prompts to prepare them for the upcoming CSP conversation.*Conversation* – The prepared patient brings the expertise of his/her lived experience to meet the CSP practitioner who is the medical expert and trained in active listening and communication skills. The quality conversation facilitates goal setting and action planning in a meaningful way to the patient.*Recording –* The CSP practitioner documents a summary of the points discussed and actionable plans in the electronic medical record (EMR). The patient is encouraged to write these plans directly on the CPL.*Actions* – The patient commits to decisions and activities that facilitate self-management through non-traditional, formal and informal support from groups and peers. The PC may be involved in referring and coordinating these efforts.*Review* – The patient attends an interim consult on a date fixed to review his/her LTCs and the progress of plans made.

